### Phase 3: individual interviews with HCPs, patients, current and bereaved carers (November 2018–July 2019)

#### Healthcare professionals

HCPs from community nursing teams, primary care, the ambulance service, the local hospices, care homes and secondary care will be invited to participate.

GPs working in practices within the CCG area will be invited to support the study and the study team will purposively sample from a list of practices, to include practices that are high-users of EPaCCS and low users of EPaCCS based on data compiled by the CCG.

The research team will purposively sample HCPs who express an interest in participating according to gender, age and profession to ensure maximum variation in the sample. All interviews with HCPs will take place over the telephone for both pragmatic and methodological reasons. Conducting interviews over the telephone will reduce the time and cost to the study that may be involved in travelling to interviews and well-planned telephone interviews can gather the same material as those held face to face.^28^

A topic guide, informed by the evolving programme theory, will be used to ensure consistency across the interviews. This will enable the research team to compare the views of each group at the stage of data analysis. Interviews will last approximately 30 min and it is anticipated that approximately 3–5 HCPs will be interviewed from each group (18–30 in total).

#### Patients, current and bereaved carers

Patients will be approached to take part in interviews through their GP surgeries or the local hospice. The research team will purposively sample from a list of practices, to include practices that are high-users of EPaCCS and low users of EPaCCS. High EPaCCS use will be defined as practices that have created greater than 20 EPaCCS records (the median number of records across all practices) 4 months post-implementation, based on data extracted by the CCG. Selected practices will be asked to identify patients, aged 18 and over, receiving EOL care, who they consider might be eligible to take part in the study.

### Inclusion criteria

Capacity to give informed consent.Aged 18 and over.Prognosis 12 months or less as identified by their GP (patient aware of this prognosis).

Potential participants will be sampled purposively to include patients across the age range, with and without an EPaCCS record, with both malignant and non-malignant health conditions.

To recruit patients to the study from the local hospice we will liaise with key clinical staff, who will be responsible for identifying appropriate patients. Once again, potential participants will be sampled purposively to include patients across the age range, with and without an EPaCCS record, with both malignant and non-malignant health conditions.

Alongside their own study information pack, all patients will be given a carer information pack which they can choose to give to their carer if they are happy for their carer to participate in the study.

GPs will also be asked to identify recently bereaved carers (between 8 weeks and 6 months of the death of their relative), who they consider might be eligible to take part in the study. GPs will be sent details of how to perform an appropriate search within EMIS Web to identify potential participants.

Interviews with carers will be conducted one-to-one with the interviewer. Interviews with patients will be conducted either one-to-one with the interviewer or in the presence of their carer, according to the wishes of the patient.

Interviews will last approximately 45 min and it is anticipated that approximately 15 patients will be interviewed (10 EPaCCS patients and 5 non-EPaCCS patients) and 10 carers (to include both current and bereaved). All interviews will be audio taped and transcribed verbatim.

### Phase 4: retrospective cohort study of routinely collected data on EPaCCS usage (March 2019–July 2019)

EMIS Web data will be accessed to identify all patients, aged 18 and over, who die in the CCG area between 22 February 2018 and 21 February 2019. Agreements are in place with the CCG to obtain this data. Patients will be identified as either having an EPaCCS record (EPaCCS patient) or not (non-EPaCCS patient), using EMIS Web coding.

EMIS Web will be used to characterise both EPaCCS and non-EPaCCS patients in terms of their gender, ethnicity and postcode (as a proxy for socio-economic status according to their Index of Multiple Deprivation Score). Data will be extracted to describe:

The proportion of patients that die with an EPaCCS record.When the EPaCCS record is initiated (ie, how many months/days prior to the patient’s death), and by whom.How frequently the EPaCCS record is updated once opened, and who makes any changes.The underlying cause and place of death for EPaCCS and non-EPaCCS patients.The number of hospital admissions and Emergency Department attendances for EPaCCS and non-EPaCCS patients in the last 12 months of life.

Descriptive data will be collected, by the CCG, on EPaCCS usage, including the number of records created by each GP surgery in the CCG area. Data from the integrated digital care record will be accessed to describe which HCPs (GPs, community nurses, hospice HCPs, ambulance HCPs and secondary care clinicians) are accessing these shared EOL care records.

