## Project methodology

### Study setting

This study will be implemented in England, where one Clinical Commissioning Group (CCG) has recently developed and rolled out an EPaCCS. This involved the dissemination of an EMIS Web template, which was circulated to general practices, to help ensure consistent data entry and coding. EMIS Web is the most widely used primary care clinical system in the UK and allows real-time patient information to be shared securely between different organisations. All practices in the CCG area are EMIS Web users and it is now also used by the local hospice and many of the community nursing teams.

The EPaCCS template was developed following extensive local clinical consultation and the National Information Standard.^23^ Although some organisations within the CCG area (ambulance service, secondary and social care) are non-EMIS Web users, information from the EPaCCS template can be viewed across the local health community, via the integrated digital care record used by health and social care professionals in the CCG area which went live at the end of February 2018. The integrated digital care record contains some of the information held at GP practices, hospital departments, community services, mental health trusts, out of hours services and local authorities across the CCG area, combining it into a single, shared digital record.

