### Conceptual framework

This study will draw on a realist evaluation approach.^24^ A randomised, experimental study design is not possible as the implementation of EPaCCS has been strongly advocated and promoted by NHS England, with 83% of CCGs in England reported to have an operational EPaCCS, or be in the planning stages, by 2013.^25^ The CCG had recently operationalised an EPaCCS at the time of study design.

By their nature, EPaCCS involve multiple organisations and a multidisciplinary style of work. It therefore requires a novel methodological approach to evaluation as described in this protocol.

Realist evaluation is a theory-driven approach designed for evaluating complex interventions, such as EPaCCS, where the outcomes are influenced by the way the intervention is delivered and in what context. Due to this complexity, any evaluation of EPaCCS seeking to determine linear causal relationships or simply find out if the intervention ‘works’ is unlikely to be useful. Pawson and Tilley,^24^ the developers of realistic evaluation, suggest that the results of an intervention (outcomes) are dependent on the introduction of appropriate reasoning and resources (mechanisms) and how these then interact with existing social and cultural condition (contexts). For the purposes of this study, we have defined context (C), mechanism (M) and outcome (O) in figure 1.

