**Figure 2 F2:**
[figure not shown]
Visual representation of the initial programme theory at a macro level. ACP, advanced care planning; EPaCCS. electronic palliative care coordination systems.

**Table 1 T1:** Programme theory for the EPaCCs study, comprising the 17 CMO statements that inform the programme theory, and the questions that will be used, in the focus group with the end-of-life board, to investigate each CMO statement

EPaCCs process	CMOs	Focus group questions
**Commissioning**	1. If the strategy behind the EPaCCs is definable, deliverable and measureable, the aim, purpose and outcomes of EPaCCS will be clear. ***(strategy)***	How will you evaluate EPaCCS success? What are the markers of success for you? What is the CCGs long term vision for the EPaCCS?
	2. If HCPs engage with the EPaCCS positively on early usage and see it as an improvement on any previous EOL register, HCPs will engage positively with EPaCCS. ***(engagement)***	Given that the previous EOL register was generally not well thought of, or used, how did the CCG plan to get HCPs on board? How do you think the EPaCCS has been received?
**Commissioning/uptake/adoption**	3. If the EPaCCS is well-publicised and marketed to all stakeholders HCPs will be aware of EPaCCS, understand the aim and purpose of the EPaCCS, and will initiate an EPaCCs template and/or access an EPaCCS record. ***(publicity)***	How was the EPaCCS publicised and marketed to different groups of HCPs? What are your views on how effective this has been? How aware do you think HCPs are of EPaCCS and do you think they understand its purpose and importance?
	4. If HCPs receive sufficient support and training, so that they know how to use it, they and will initiate an EPaCCs template and/or access an EPaCCS record. ***(training)***	Can you tell us about the CCG strategy for providing training and support to different groups of HCPs in the EPaCCS roll-out? What do you think about this, and how effective it has been?
**Uptake/adoption**	5. If HCPs have the time and/or resources to learn a new system, an EPaCCS template will be initiated. ***(time and resources)***	There are a significant number of GP practices that have not initiated an EPaCCS – do you have any thoughts about why this might be? Do you think all HCPs will have the time and resources (ie, they are connected to a computer, have internet and NHS network access) to learn and new system and access EPaCCS?

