### Phase 5: data analysis and synthesis of study findings (October 2018–October 2019)

#### Quantitative methods

Quantitative data will be analysed using Stata V.15 and reported using descriptive statistics. Within the context of this realist evaluation, we were keen to use the quantitative data to address a single hypothesis, namely whether nominal possession of an EPaCCS record was associated with increased chance of dying at home. However, logistic regression will be used to determine the adjusted OR and 95% CI for the associations between having an EPaCCS record and dying at home, considering other factors of interest, including, but not limited to: age, sex, deprivation and underlying cause of death.

Of approximately 8000 deaths occurring in the CCG area over the year of study, we expect around 10% (800 deaths) of patients to have an EPaCCS.^10^ If the proportion of deaths occurring at home is expected to be 25% among those without an EPaCCS, we would have over 99% power to detect an absolute increase of 10% to 35% among those with an EPaCCS. The power would be about 84% if the proportion were increased by 5% to 30%.

Descriptive statistics will be employed to report EPaCCS usage.

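### The one-year death window appears to open at about EPaCCS roll-out, so having a record probably rises with date of death, and the home-death model commits to no calendar term

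*Protocol article*

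**What the plan says.** Phase 4 of the protocol article defines the cohort by date of death: patients "who die in the CCG area between 22 February 2018 and 21 February 2019". Exposure is a yes/no flag: "Patients will be identified as either having an EPaCCS record (EPaCCS patient) or not (non-EPaCCS patient), using EMIS Web coding".

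The article places the start of the system as follows:
- Study setting says that the CCG "has recently developed and rolled out an EPaCCS". It dates only the integrated digital care record, through which organisations not using EMIS Web view the template, "which went live at the end of February 2018".
- Conceptual framework adds: "The CCG had recently operationalised an EPaCCS at the time of study design". The patient and public involvement section puts discussion of the outline proposal in April 2018.
- On early uptake, the Phase 3 section defines high users as "practices that have created greater than 20 EPaCCS records (the median number of records across all practices) 4 months post-implementation". A focus-group question in Table 1, for the October 2018 focus group, begins "There are a significant number of GP practices that have not initiated an EPaCCS".

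Quantitative methods plans a logistic regression of dying at home on having a record, with other factors "including, but not limited to: age, sex, deprivation and underlying cause of death". Date, month or season of death is not named. Power is given for about 8000 deaths, 10% of them with a record, and 25% home deaths without one: over 99% for 35% and about 84% for 30%.

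**The concern.** If records were being introduced as the window opened, a person who died in its first weeks had only weeks in which to acquire one, while a person who died near its end had up to a year. Deaths with a record would then fall later in the year than deaths without. The window covers each season once, so stage of roll-out, season and any change in local services would all move together with exposure.

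If the share of deaths at home also changed over those months, for whatever reason, part of that change would appear in the EPaCCS odds ratio. Age, sex, deprivation and cause of death would not reliably remove it. This affects the one hypothesis that the quantitative arm sets out to test, and the direction cannot be known in advance.

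**Working it through.** **1. The plan's own figures.** Inputs from Quantitative methods: 7200 deaths without a record, 800 with, 25% v 30% at home. Two-sided 5% is assumed, as the article states no alpha for the power. Unpooled: SE = √(0.25×0.75/7200 + 0.30×0.70/800) = 0.0170; 0.05/0.0170 − 1.96 = 0.98; power 83.7%. Pooled, continuity-corrected and arcsine versions give 85.8%, 84.8% and 85.3%. For 35%, every version exceeds 99.9%. The stated power reproduces and is not in question. The implied odds ratios are (0.30/0.70)/(0.25/0.75) = 1.29 and (0.35/0.65)/(0.25/0.75) = 1.62.

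**2. Does exposure rise with date of death?** The window opens on 22 February 2018. The only dated go-live is the end of that month, the system was recent at study design, and a question prepared for October 2018 still speaks of many practices with no record. This makes a rise very likely. No monthly prevalence is given, so its shape has to be assumed.

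**3. One worked case (assumed).** Let the chance of a record rise in a straight line, e = 0.2×(m − 0.5)/12 in month m, mean 10%, with equal deaths per month.
- Share of deaths with a record in months 7–12: 54/72 = 75.0%.
- Share of deaths without a record in months 7–12: 5.1/10.8 = 47.2%.
- False difference = (0.750 − 0.472) × d = 0.278d, where d is the difference in home-death share between the two halves of the year.
- d = 3 points gives 0.83 points (OR 1.045); d = 5 points gives 1.39 points (OR 1.076).

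**4. A range of cases (assumed).** Twelve monthly strata, no true effect, mean uptake about 10%, 25% home deaths, ±12% winter variation in deaths. Home-death share either has a trend of up to 4 points over the year or a seasonal amplitude of up to 3 points, taken at its least favourable timing.

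| Uptake shape | Spurious OR without a month term |
|---|---|
| Flat | 1.00 |
| 4-month rise, then plateau | 0.97–1.03 |
| Straight line | 0.94–1.06 |
| Late-accelerating | 0.91–1.09 |

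**5. Against the study's precision.** SE of the log OR at 25% home deaths = √(1/(800×0.25×0.75) + 1/(7200×0.25×0.75)) = √(1/150 + 1/1350) = 0.086. Since ln 1.09 = 0.086, the upper extreme is about one standard error. A two-sided 5% test would then have a true error rate of about 8% at OR 1.045, 14% at 1.076 and 17% at 1.09.

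**6. Cost of a month term.** Let R² be the share of the variance of exposure explained by month. Information on exposure falls from 8000×0.1×0.9 = 720 to 720×(1 − R²). Power for 30% v 25% is Φ(0.05/√(0.255×0.745/information) − 1.96), which is 86.8% without the term. Holding deaths with a record at 800:
- plateau shape, R² 0.014: 86.4%
- straight line, R² 0.038: 85.5%
- late-accelerating, R² 0.086: 83.7%

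The loss is about 0.5 to 3 points. It reads as under 2 points (84.9% to 86.2%) if the late-rising shapes are also allowed slightly more than 800 deaths with a record. Power for 35% stays above 99.9%.

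**The case against.** A reader might infer that almost nobody had a record when the cohort opened. The documents do not say so. The end-of-February date belongs to the shared viewing record, whereas exposure is an EMIS Web code created through a template whose roll-out is called only recent. The one uptake figure points to a fairly quick start: a median of 20 records at 4 months means at least half of practices held 20 or more, hence at least about 10 records per practice overall. The number of practices is not given; if it were 50 to 100 (an assumption), that is at least 500 to 1000 records by then, and quick uptake followed by a plateau gives only 0.97 to 1.03. This weakens the steeper shapes but does not remove the point. Records created are not deaths with a record. They are meant for people in roughly the last year of life, so exposed deaths lag behind record creation.

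A reader might also infer that the plan rules out a calendar adjustment. It does not: the covariate list is expressly open, and an article may leave the full list to a fuller document. That stands. But every named factor describes the patient, whereas this confounder arises from the window itself, and an open list does not commit to handling it.

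The article asks about association with nominal possession and disclaims linear causal claims. That is fair. An adjusted odds ratio is still meant to be read with the obvious competing explanations removed.

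**Conclusion.** The point holds as a moderate design improvement; it is not an error in the plan's arithmetic. The window appears to start at about roll-out, record possession very likely rises with date of death, and nothing named in the model separates the two.

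Whether this biases the result is not shown. It needs both rising uptake and a change in home-death share over the same months, and the documents give no monthly figure for either. Under the assumed ranges the spurious odds ratio is about 0.91 to 1.09. That would not by itself imitate the planned 1.29, but at up to about one standard error it could noticeably distort the test or mask part of a real association. A reader should not conclude that an observed EPaCCS association would be an artefact of calendar time; the documents do not support that.

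**What to change.** - Name calendar month of death (or quarter) as a categorical covariate in the home-death logistic regression, so that deaths with and without a record are compared within the same period.
- State the template's roll-out date and report the proportion of deaths with a record by month of death.
- If that proportion is low in the earliest months, repeat the model without them as a sensitivity analysis. Let the observed prevalence decide how many months to drop.

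Date of death already defines the cohort, so no new data are needed. Month adds 11 parameters in about 8000 deaths, at the small cost in power shown above; quarter adds 3. The rest is one descriptive table and at most one further model run.

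### The Phase 4 cohort is defined by where death occurs, not by practice registration, so entry depends on something closely tied to the outcome, dying at home

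*Protocol article*

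**What the plan says.** The Phase 4 section of the protocol article sets the source and the entry rule in one sentence: "EMIS Web data will be accessed to identify all patients, aged 18 and over", restricted to those "who die in the CCG area between 22 February 2018 and 21 February 2019". Exposure comes from the same system: "Patients will be identified as either having an EPaCCS record (EPaCCS patient) or not (non-EPaCCS patient), using EMIS Web coding".

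The Quantitative methods section names a single hypothesis, that possession of a record is associated with dying at home. For this, "logistic regression will be used to determine the adjusted OR and 95% CI for the associations between having an EPaCCS record and dying at home", with covariates "including, but not limited to: age, sex, deprivation and underlying cause of death". Its sample-size paragraph begins "Of approximately 8000 deaths occurring in the CCG area over the year of study". It expects 10% (800) to have a record and 25% home deaths without one, and gives power of over 99% for 35% with a record and about 84% for 30%.

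Neither section requires that the person be registered with a CCG practice or live in the area. Study setting states that "All practices in the CCG area are EMIS Web users".

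**The concern.** Where a person dies helps to decide whether they enter the cohort, and where they die is also the outcome. For a patient of a CCG practice, a death at home will normally be inside the area. A death in a hospital, hospice or care home may not be. Applied as written, the rule therefore tends to remove non-home deaths of people who belonged to the population that could have had a record.

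Two results are exposed. The first is the description of place of death in each group, which the first aim compares, together with the proportion of patients who die with a record. The second is the adjusted odds ratio, if out-of-area deaths are lost at different rates with and without a record. Different rates are plausible: a record reflects a recognised end-of-life phase with planned local care, and an unexpected death away from home is less likely to have one. The listed covariates do not include geography.

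The Background section itself reports that earlier gains in home deaths may reflect selection, because hospital deaths went uncaptured. The entry rule should not open another route to the same problem.

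**Working it through.** **Inputs from the Quantitative methods section.** 8000 deaths, 800 with a record and 7200 without; home deaths 25% without a record, 30% or 35% with one. The significance level is not stated; two-sided 5% is assumed.

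**The plan's own figure first (25% v 30%).**
- Pooled proportion: (0.25 × 7200 + 0.30 × 800)/8000 = 0.255.
- Standard error under the null: √[0.255 × 0.745 × (1/7200 + 1/800)] = 0.01624.
- Standard error under the alternative: √[0.25 × 0.75/7200 + 0.30 × 0.70/800] = 0.01699.
- Power, pooled: Φ[(0.05 − 1.96 × 0.01624)/0.01699] = 85.8%. With continuity correction it is 84.8%, and unpooled 83.7%.
- For 25% v 35%, power is above 99.9% in every variant.

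The stated figures of about 84% and over 99% are reproduced. The issue is eligibility, not the power arithmetic.

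**Effect on the proportions.** If a share L of all deaths in a group is lost, all of them non-home, the home-death proportion p becomes p/(1 − L). With p = 25% and L = 5%: 0.25/0.95 = 26.3%.

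**Effect on the odds ratio.** Let e0 and e1 be the fractions of *non-home* deaths lost without and with a record, all home deaths being kept. The observed proportion is p/[p + (1 − p)(1 − e)], and the odds of home death in a group become p/[(1 − p)(1 − e)]. Hence

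observed OR = true OR × (1 − e0)/(1 − e1).

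The same factor applies within covariate strata, with e0 and e1 taken within the stratum. From 25% v 30%, the true OR is (0.30/0.70)/(0.25/0.75) = 1.286. Every loss fraction below is an assumption.

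| e0 | e1 | Home, no record | Home, record | Difference (points) | Factor | Observed OR |
|---|---|---|---|---|---|---|
| 0 | 0 | 25.0% | 30.0% | 5.0 | 1.000 | 1.286 |
| 5% | 5% | 26.0% | 31.1% | 5.1 | 1.000 | 1.286 |
| 10% | 10% | 27.0% | 32.3% | 5.2 | 1.000 | 1.286 |
| 5% | 0 | 26.0% | 30.0% | 4.0 | 0.950 | 1.221 |
| 10% | 2% | 27.0% | 30.4% | 3.4 | 0.918 | 1.181 |
| 20% | 5% | 29.4% | 31.1% | 1.7 | 0.842 | 1.083 |
| 2% | 10% | 25.4% | 32.3% | 6.9 | 1.089 | 1.400 |

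The 26.3% above and the 26.0% in the table differ because the first takes 5% of all deaths and the second 5% of non-home deaths; 5% of all deaths is 0.05/0.75 = 6.7% of non-home deaths.

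With no true association (25% in both groups) the observed OR equals the factor, so these unequal losses give 0.842 to 1.089.

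**The case against.** The strongest reply is that the authors probably meant registered patients. The extract comes from EMIS Web, a primary care system used by every practice in the area. Exposure, ethnicity and postcode come from the same records, and the article also uses the words about the CCG area to describe practices. An article condenses a fuller protocol, and no filter on the geography of death is described. This stands as a plausible account of intent. It does not settle the matter, because no sentence says it and the rule is given twice in terms of where death occurs. An extraction that followed the text would give the worse cohort.

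It is also fair that outcome-related inclusion does not by itself bias an odds ratio, that the listed covariates may absorb some differential loss, and that the documents hold no evidence of such loss.

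A reader might infer more than the documents support:
- *That the rule removes only non-home deaths.* A registered patient living just across the boundary who dies at home would also be dropped, and the documents do not say how a death at a relative's house outside the area would be classed.
- *That the association is necessarily shrunk.* That assumes more loss without a record. The reverse pattern inflates it.
- *That people registered elsewhere who die in the local hospice enter as deaths without a record and inflate the association.* Study setting says of EMIS Web that "it is now also used by the local hospice and many of the community nursing teams", but nothing says that hospice-held records of such people will be extracted. It is a possibility only, with no number attached.
- *That the power statement is wrong.* It reproduces, and the 8000 is given as approximate.

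**Conclusion.** The point holds as a defect in the stated entry rule. As written, inclusion depends on the location of death, which is closely tied to the outcome, and CCG patients who die outside the area are lost. The descriptive home-death proportions shift upward even with equal loss, by 1.3 points in the 5% example, on the assumption that all lost deaths are non-home. The odds ratio is biased only if loss differs by EPaCCS status given the covariates, by the factor (1 − e0)/(1 − e1). Neither size nor direction can be determined from the documents, and if out-of-area deaths are few the effect is small. The point justifies changing the sentence because the change is nearly free. It does not show that the home-death comparison is biased in fact.

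**What to change.** In Phase 4, define the cohort as all adults registered with a CCG practice at the date of death who died between 22 February 2018 and 21 February 2019, wherever death occurred. Use the same definition for the denominator of the proportion dying with an EPaCCS record. Report the number of out-of-area deaths by EPaCCS status, so that readers can see how much the choice matters. The power figures can stay as they are.

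The cost is one sentence in the protocol, one condition in the extraction query and one line in the results, ideally settled before Phase 4 starts in March 2019. No new data source is needed, since all practices in the area already use the system. If registered patients were intended all along, the same sentence simply corrects the wording.
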